### 2.5. Procedures and interventions

#### 2.5.1. Health status and antropometric data.

The participants will be interviewed for health status, smoking status, previous medical examinations, and demographic data. Anthropometric data were recorded using a previously calibrated Welmy scale (Model: 110 CH G, Welmy, Brazil). The body mass index (BMI) was calculated.

#### 2.5.2. The DASS-21: depression, anxiety, and stress scale.

We used the public domain DASS-21 questionnaire to characterize perceived depression, anxiety, and stress. This instrument has 21 questions with a 0 to 4 Likert scale, is validated for the Portuguese language, and shows high internal consistency (Cronbach’s alpha was.92 for depression,.90 for stress, and.86 for anxiety).^[48]^

#### 2.5.3. The brief medication questionnaire (BMQ): adherence.

This questionnaire was intended to assess adherence to pharmacological treatment with antihypertensive medications. This instrument has been validated for the Brazilian Portuguese language and is in the public domain, with 80% sensitivity and 100% specificity in the regimen domain.^[49]^ The BMQ in its validated Brazilian version was superior to the Morisky-Green questionnaire.^[49]^

#### 2.5.4. Preparatory briefing about HT and meditation.

On the 1^st^ visit, the subjects allocated to both groups will be invited to an introductory explanation of hypertension after laboratory instrument familiarization. A researcher not directly involved in lab data collection will introduce fundamental knowledge about essential hypertension, the autonomous nervous system, and treatment. The CG will only receive information about hypertension and the meditation group will receive an additional preparatory briefing about meditation during the 1^st^ meditation session.

#### 2.5.5. Familiarization.

During the 1^st^ visit, all randomized subjects will be invited to the laboratory to perform several normoxic BP measurements using naso-oral masks and accessories under paced breathing. Submaximal testing (up to Borg 5) with a cycle ergometer will also be performed with a naso-oral mask intended to desensitize discomfort.

#### 2.5.6. RVV.

During the 2^nd^ visit, the subjects will be admitted to a climatized lab room at ~7:00 hours after a light breakfast without stimulant foods and will be instructed to remain calm during the study protocol. They will be monitored using a QUARK metabolic system (QUARK CPET, COSMED, Rome, Italy, 2016) for breath-by-breath oxygen consumption (*V*´O_2_), minute ventilation (*V*´_E_), tidal volume (*V*_T_), breathing frequency (*f*R), end-tidal carbon dioxide (*P*_ET_CO2), and inspiratory/expiratory time (s) using a low-resistance calibrated turbine (COSMED, Rome, Italy, 2016). The analyzer was calibrated with 2-point precision gases (GAMA GASES, São Paulo, Brasil). The turbine was attached to a non-rebreathing 2-way valve connected to a naso-oral mask attached to the head with head straps (Hans-Rudolph Inc., USA, 2036 series, 2019). All trials will be registered in real time and saved for posterior analysis in accordance with previously published methods.^[50]^ Resting variability was measured using our previously described method.^[51]^ First, a non-linear evaluation of breath-by-breath signals using an *in house* Poincaré analysis algorithm will be performed using the “R^®^” free software program (http://www.R-project.org/) to calculate SD1 and SD2 for minute ventilation, tidal volume, and breathing frequency. The resting trial was performed in a seated position for 5 min (Protocol 1, Fig. 3).

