## 1. Introduction

### 1.1. Background and rationale

Systemic arterial hypertension (HT) was the leading cause of cardiovascular mortality in 2010.^[1]^ Although the latest american college of cardiology & american heart association (2018) guidelines on HT do not recommend meditation,^[1]^ this opinion is not shared by the American Heart Association^[2,3]^ and the International Society of Hypertension.^[4]^ However, the mechanisms underlying these effects are largely unknown.

Meditation can modulate the autonomic nervous system (ANS),^[5–8]^ although a recent meta-analysis did not support this premisse.^[9]^ Herein, we propose a role for the carotid body (CB), the principal oxygen chemoreceptor in humans, playing crucial functions in maintaining respiratory, cardiovascular, and neurohumoral homeostasis.^[10]^ The rationale for this hypothesis is supported by the meaningful nerve connections between the CB, hypothalamic areas, and *nucleus tractus solitarii*,^[11–14]^ with a prevailing effect on increasing sympathetic activity in normoxic conditions due to abnormal hypertonicity in HT.^[12,14]^ In fact, there is some evidence of a link between meditation and balance of neurotransmitters in the hypothalamus.^[15–17]^ We speculate that the connection between meditation, the hypothalamus-pituitary-adrenal axis (HPA), and CB activity would involve stabilization of the HPA axis, as has been proposed with respect to yoga^[18–20]^ or transcedental meditation^[21]^–and a highly coordinated engagement of brain structures such as the prefrontal cortex, amygdala, and hippocampus (hyperachical-dependent activity). Of note, the prefrontal cortex, amygdala, and hippocampus gray matter have been shown to change with yoga/meditation.^[22–25]^ Interestingly, hypertonicity of the CB^[12,26–29]^ and increased size and weight of the CB^[30–35]^ are common findings in HT. However, inconsistent evidence has revealed a decrease in systemic blood pressure (BP) through CB deactivation in response to hyperoxia in hypertensive subjects,^[36–38]^ suggesting that hyperactivity of the CB may be mechanistically associated with sympathetic dysregulation.^[12,39]^ In addition, CB and BP are closely linked to ventilatory variability,^[40–42]^ and lifestyle interventions can reduce ventilatory variability during exercise.^[43]^ Acute changes in breathing variability have also been demonstrated during meditation.^[44]^

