#### 2.5.7. BP measurements.

Blood pressure will be measured based on replicated tests under the same described metabolic and ventilatory RVV monitoring. The arm was positioned at the heart level, and the NHT sequence was preceded by baseline BP measures (3x, 1-minute apart) immediately after the 5-minutes RVV acquisition (Protocol 1, Fig. 3). The target is a minimum of 3 BP measures differing within < 5 mm Hg and no BP measure differing within > 10 mm Hg^[1,52]^ between 3, 1-min apart, successive oscillometric measurements (Multiparametric Monitor, Dixtal-Philips^®^, Manaus, Brazil, 2015). The measurements will be preceded by a 3 to 4 minutes recovery only for hyperoxic trials, ensuring that the BP and *P*_ET_O_2_ return to the baseline value. Aditional measurements will be performed only if the first 2 readings differ by > 10 mm Hg, and BP will be recorded as the average of the last 2 readings.^[1]^ The noninvasive blood pressure (NIBP) system was properly calibrated at regular 3-month intervals using an NIBP simulator (Comprehense NIBP simulator^®^, Brazil, 2018). The trials will be repeated during normoxic and subsequently hyperoxic gas delivery to avoid residual effects of CB deactivation under normoxic conditions. The lights will be dimmed to ensure stable measurements and no interaction with the participants will occur during the assessment.

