#### 2.5.8. NHT.

The NHT will be performed under paced breathing frequency (20 breaths minute^-1^) with controlled inspiratory time (duty cycle ~ 0.3) throughout metronome pacing using incentive screens (Bounce Metronome, USA, 2015). Pacing breathing is important to avoid lower respiratory frequency and baroreceptor modulation with an acute reduction in blood pressure, as suggested in essential hypertension.^[53]^ The NHT will be performed through 21% or 100% FIO_2_ (in this order) through gas cylinders (White-Martins™, Campo Grande, MS, Brazil), delivered through a Douglas bag connected to a *Y*-shaped 2-way non-rebreathing valve (Hans-Rudolph Inc., USA, 2036 series, 2019) during 30 to 40 seconds trials, because previous studies have shown that the CB hyperoxic deactivation effect in BP is lost after this time, presumably due to systemic arterial intimal oxidative stress, which rebounds vasoconstriction^[27,36]^; Of note, the time delay for oscillometric BP measurement is reliably between 30 to 40 seconds for our chosen device. The participants will be permitted breaks from paced breathing between interventions (Protocol 2, Fig. 3).

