#### 2.5.11. Transcedental meditation (TM).

Transcendental meditation follows previously explored methods.^[58,59]^ A certified trainer will teach the TM technique to the group in the standard 4-day course preceded by an introductory briefing. The subjects will be widely informed about the method, receiving a 1-hour group-based introductory briefing about the method in the 1st session, followed by a personal interview, personal instruction session, and group verification sessions on 3 consecutive days following personal instruction. To verify the correctness of TM practice, group-based TM sessions will be performed once a week, guided by a senior professional therapist in a 20-minutes session in an appropriate and comfortable room while sitting comfortably with their eyes closed. During the week, the subjects will be trained to perform 2 20-minutes unsupervised sessions at home each day. TM will be implemented in a more cognitive fashion, with passive mental focusing associated with slow breathing. Predefined weekly contact by phone will be performed to check for adherence and adverse effects.

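### Week-8 RVV, RCBA and pre-NHT baseline BP are taken in calm rest with no breathing control described, so meditating or slow breathing at the test could not be told apart from a lasting 8-week effect

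*Protocol article*

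**What the plan says.** The objective is change after 8 weeks of TM compared with control (1.2, 2.6.1, 2.6.2). RCBA and BP under normoxia and hyperoxia are primary outcomes; RVV is secondary.

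Test conditions at visit 2, repeated at week 8:

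- **RVV (2.5.6).** Admission is at about 7:00, and participants "will be instructed to remain calm during the study protocol". On the recording itself: "The resting trial was performed in a seated position for 5 min". No pacing is described.
- **Baseline BP (2.5.7).** "the NHT sequence was preceded by baseline BP measures (3x, 1-minute apart) immediately after the 5-minutes RVV acquisition". No pacing is described for these readings. For the BP session: "The lights will be dimmed to ensure stable measurements and no interaction with the participants will occur during the assessment".
- **NHT BP (2.5.8).** "The NHT will be performed under paced breathing frequency (20 breaths minute^-1^) with controlled inspiratory time", guided by a metronome on screens. The reason given is: "Pacing breathing is important to avoid lower respiratory frequency and baroreceptor modulation with an acute reduction in blood pressure".
- **RCBA (2.5.9).** Five minutes of calm breathing on room-level oxygen, then 1 minute of 100% oxygen, done three times. No pacing is described.

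On the intervention, 2.5.11 says: "TM will be implemented in a more cognitive fashion, with passive mental focusing associated with slow breathing". It is practised seated with eyes closed, and at home in two 20-minute sessions a day. On acute effects, 1.1 says: "Acute changes in breathing variability have also been demonstrated during meditation".

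**The concern.** At week 8 only the TM arm has been trained in a seated, quiet technique with slow breathing. The unpaced resting tests are seated or calm, and participants are told to stay calm. The conditions described neither discourage use of the technique nor set an interval since the last practice.

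The protocol recognises the hazard for BP and controls breathing in the NHT. RVV and RCBA are computed from ventilation itself, yet no equivalent safeguard is described for them. Pacing would not suit these measurements, so the natural control is an instruction on behaviour.

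Two readings of the results are at stake:

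- A between-arm difference in RVV or RCBA could be a state at the time of the test, a lasting effect of training, or both.
- Section 2.10 correlates change in RCBA with changes in RVV, EVV and BP to explore effects after meditation. RCBA and RVV both come from the ventilation signal, so one acute breathing state could move both and contribute to a correlation read as a carotid-body mechanism.

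**Working it through.** The plan gives no figure on this point, so there is none to reproduce. The check is mainly a comparison of the stated conditions.

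**Step 1: breathing control by measurement**

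| Measurement | Outcome level | Breathing control described | Open to slow breathing at the test? |
|---|---|---|---|
| RVV (2.5.6) | Secondary | None | Yes |
| Baseline BP before NHT (2.5.7) | Not listed separately as an outcome | None | Yes |
| NHT BP (2.5.8) | Primary | 20 breaths/min, timed inspiration | No, during readings |
| RCBA (2.5.9) | Primary | None; stable ventilation required | Yes |

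Section 4 confirms the boundary: the aim of keeping a similar ventilatory pattern before and after meditation is stated for the BP measurements.

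**Step 2: who can be affected**

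Only the TM arm is taught the technique, and regular meditators are excluded at entry (2.4.3). Any acute use would therefore fall almost entirely in one arm at one time point, and the between-arm comparison of change does not cancel it.

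**Step 3: would it be noticed?**

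Lab staff are blinded, and conversation that could reveal the group is barred (2.4.5). Section 2.5.11 gives no clock time for home sessions, so the interval between the last session and a 7:00 admission is unknown. Weekly calls record adherence, not use on the test day.

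**Step 4: sensitivity of the comparison (assumed shifts)**

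Inputs: 30 per arm and two-sided 0.05 (2.4.6); true 8-week effect zero; average acute shift *d*, in SD units, over the whole TM arm. If a fraction *p* uses the technique and each user shifts by *a*, then *d* = *p* × *a*.

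Standard error = √(2/30) = 0.258. P(significant) = Φ(*d*/0.258 − 1.96) + Φ(−*d*/0.258 − 1.96).

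- *d* = 0.2: Φ(−1.185) + Φ(−2.735) = 0.12
- *d* = 0.5: Φ(−0.024) + Φ(−3.90) = 0.49
- *d* = 0.8: Φ(1.14) + Φ(−5.06) = 0.87

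For the unpaced baseline SBP readings only, with average shifts of 1, 2 and 3 mm Hg:

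- SD 4.2 (pilot, 2.4.6): standard error 4.2 × 0.258 = 1.08; probabilities 0.15, 0.45, 0.79
- SD 4.2 × √2 = 5.94: 0.10, 0.26, 0.50
- SD 8 (assumed): 0.08, 0.16, 0.31

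The pilot SD comes from 12 normotensive or prehypertensive people on two trial days. A larger SD over 8 weeks in hypertensive participants is plausible, hence the range.

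**The case against.** The strongest case against has five parts.

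- **BP is already handled.** The primary BP outcomes are the NHT readings, which are paced on a screen for 30 to 40 seconds after familiarization with paced breathing (2.5.5). This stands. A reader might infer that the primary BP result is compromised in the same way, but the documents do not support that. Pacing does not exclude a mental state, a session just before the visit, or carry-over from the permitted breaks. Those are residual possibilities, and the finding does not rest on them.
- **A masked 5-minute recording is not a TM session.** No test states that eyes are closed, and dimmed light and silence are specified only for the BP session. This stands in part. The resemblance is incomplete, but slow breathing needs neither closed eyes nor darkness.
- **Direction is unknown.** A reader might infer a bias towards the hypothesis. The article predicts no direction for ventilatory variability, and nothing shows which way a meditative state would move the ventilatory fall under oxygen. This stands; the problem is attribution, not a known direction.
- **It is only missing detail.** An article may leave participant scripts to the full protocol. This limits the strength of the point but does not remove it. The article specifies arrival time, breakfast, posture, lighting and interaction, and it confines breathing control to BP while naming the acute effect on breathing variability.
- **The remedy has its own risks.** Naming meditation to everyone could cue participants who are blinded to the hypotheses, and dropping users from the analysis removes people from one arm after randomisation. Both points stand and shape the fix.

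**Conclusion.** The point holds for RVV, RCBA and the unpaced baseline BP readings. Under the stated conditions, an acute state in TM participants could not be separated from a lasting 8-week effect, and it could contribute to the correlation between change in RCBA and change in RVV.

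It is tempting to go further and say that an acute state is what week 8 records, or that one breathing state drives RVV, RCBA and BP together. The documents show that the first could happen, not that it does or how often. The second fails for NHT BP, where breathing rate is imposed. EVV is measured during exercise at a separate visit and is outside this point.

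The size is unknown. The probabilities above rest on assumed shifts and a normal approximation. They show only that a moderate average shift of 0.5 SD would give a significant result about half the time with no lasting effect. The article does not say how the baseline BP readings enter the analysis, so the main weight falls on RCBA, as a primary outcome, and then on RVV.

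**What to change.** In 2.5.6, 2.5.7 (baseline BP) and 2.5.9, add one neutral scripted instruction, identical in both arms and at every test visit. It should ask participants to breathe spontaneously with eyes open, and to use no meditation, relaxation or deliberate breathing technique on the morning of the visit before testing or during the tests.

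Have a researcher outside the blinded lab team record the time of the last TM session and any use of a technique during testing.

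Keep the intention-to-treat comparison as the main analysis. Report any analysis by reported use as supportive only, because it excludes participants from one arm after randomisation and no longer compares the randomised groups.

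Cost: one script and two questions per visit. The TM arm delays one home session on test days. The script must be worded so that it does not reveal the study hypotheses; listing several techniques together helps. Lab blinding is kept because the script is the same for everyone and the answers stay outside the lab team.

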**Figure 3. F3:**
[figure not shown]
Data collection timeline at the lab scheduled before allocation and repeated upon intervention completion. BP= blood pressure, v = variability, RCBA = resting carotid body activity, CPET = cardiopulmonary exercise testing.

#### 2.5.7. BP measurements.

Blood pressure will be measured based on replicated tests under the same described metabolic and ventilatory RVV monitoring. The arm was positioned at the heart level, and the NHT sequence was preceded by baseline BP measures (3x, 1-minute apart) immediately after the 5-minutes RVV acquisition (Protocol 1, Fig. 3). The target is a minimum of 3 BP measures differing within < 5 mm Hg and no BP measure differing within > 10 mm Hg^[1,52]^ between 3, 1-min apart, successive oscillometric measurements (Multiparametric Monitor, Dixtal-Philips^®^, Manaus, Brazil, 2015). The measurements will be preceded by a 3 to 4 minutes recovery only for hyperoxic trials, ensuring that the BP and *P*_ET_O_2_ return to the baseline value. Aditional measurements will be performed only if the first 2 readings differ by > 10 mm Hg, and BP will be recorded as the average of the last 2 readings.^[1]^ The noninvasive blood pressure (NIBP) system was properly calibrated at regular 3-month intervals using an NIBP simulator (Comprehense NIBP simulator^®^, Brazil, 2018). The trials will be repeated during normoxic and subsequently hyperoxic gas delivery to avoid residual effects of CB deactivation under normoxic conditions. The lights will be dimmed to ensure stable measurements and no interaction with the participants will occur during the assessment.

#### 2.5.8. NHT.

The NHT will be performed under paced breathing frequency (20 breaths minute^-1^) with controlled inspiratory time (duty cycle ~ 0.3) throughout metronome pacing using incentive screens (Bounce Metronome, USA, 2015). Pacing breathing is important to avoid lower respiratory frequency and baroreceptor modulation with an acute reduction in blood pressure, as suggested in essential hypertension.^[53]^ The NHT will be performed through 21% or 100% FIO_2_ (in this order) through gas cylinders (White-Martins™, Campo Grande, MS, Brazil), delivered through a Douglas bag connected to a *Y*-shaped 2-way non-rebreathing valve (Hans-Rudolph Inc., USA, 2036 series, 2019) during 30 to 40 seconds trials, because previous studies have shown that the CB hyperoxic deactivation effect in BP is lost after this time, presumably due to systemic arterial intimal oxidative stress, which rebounds vasoconstriction^[27,36]^; Of note, the time delay for oscillometric BP measurement is reliably between 30 to 40 seconds for our chosen device. The participants will be permitted breaks from paced breathing between interventions (Protocol 2, Fig. 3).

#### 2.5.9. RCBA.

Resting CB activity will be measured through a hyperoxic trial (FIO_2_ = 100%) after ensuring stable minute ventilation (5-minutes of normoxic calm breathing). Baseline minute ventilation is the average value of the last 60 seconds of breath-by-breath stable ventilatory signal. During the next 1-minute hyperoxic trial delivered through a non-rebreathing system, the nadir of 10 seconds averaged minute ventilation was measured.^[54]^ The test was repeated 3 times (3-minutes apart), and the average value was considered (Protocol 3, Fig. 3). The lowest value is taken as an index of basal CB activity, and a greater reduction in minute ventilation corresponds to a greater tonic input from the carotid body.^[54]^

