#### 2.6.1. Primary outcomes.

The primary outcomes were as follows:(i)BP changes under normoxia.(ii)BP changes under hyperoxia, and.(iii)changes in RCBA after 8 weeks of TM compared with control subjects. Any BP difference for normoxic or hyperoxic trials > ± 5.9 mm Hg, as determined by our reliability study, after 8 weeks will be considered a clinically significant result (Figure S2 and S3, Supplemental Digital Content, http://links.lww.com/MD/I272). To the best of our knowledge, there has been no reproducibility study of the RCBA in adults with hypertension.

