### 2.10. Statistical analysis plan

The 2 groups will initially be compared at baseline in terms of their characteristics, using the chi-squared test for categorical variables and *t*-tests for continuous measures, after Shapiro–Wilk tests for normality. Descriptive analysis will be performed using frequencies and percentages to obtain clinical, anthropometric, and sociodemographic conditions. Two-way ANOVA for repeated measurements will be applied considering between-factors (2 groups) as independent variables and 2 within-factors for BP measurements (gas type and time) as dependent variables (pre-normoxic, pre-hyperoxic, post-normoxic, and post-hyperoxic). A mixed-design with repeated measures will be applied for RCBA, RVV, and EVV as dependent variables in comparing week “0” with week “8.” A post hoc analysis using the Bonferroni procedure, taking into account standard sphericity, will be performed. If this criterion is violated through the Mauchly test, we use the Greenhouse-Geisser correction. In order to explore possible change effects after meditation, coefficients of correlation through Pearson product-moment, including ∆ BP, ∆RVV and ∆ EVV as dependent variables and, ∆RCBA as independent variable, will be performed as percentage of change (∆= (“8 week–“0 week/0 week”)_ *_ 100. Effect sizes (Cohen-d) will also be presented to show the magnitude of our findings, using the scores of 0.20 as small, 0.50 as a medium, and 0.80 as large. Statistical Package for Social Sciences software (version 17.0; IBM Corp, Armonk, NY) was used for all statistical analyses. The study will adopt a *P-value* ≤ 0.05 as statistically significant.

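### The primary RCBA index is not defined in one way, and its contrast of a 60-second mean with a 10-second nadir rises with breathing variability whether or not carotid body activity changes

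*Protocol article*

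**What the plan says.** Section 2.6.1 lists as the third primary outcome "changes in RCBA after 8 weeks of TM compared with control subjects". Section 2.5.9 describes the measurement:

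- Before hyperoxia: "Baseline minute ventilation is the average value of the last 60 seconds of breath-by-breath stable ventilatory signal".
- During one minute of 100% oxygen: "the nadir of 10 seconds averaged minute ventilation was measured".
- Combining the repeats: "The test was repeated 3 times (3-minutes apart), and the average value was considered".
- The index: "The lowest value is taken as an index of basal CB activity".
- How it is read, in the same sentence as the index: "a greater reduction in minute ventilation corresponds to a greater tonic input from the carotid body".

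The RCBA test follows unpaced calm breathing; paced breathing is described only for the normoxic and hyperoxic BP trials (section 2.5.8). Resting and exercise ventilatory variability (RVV, EVV) are the secondary outcomes (section 2.6.2). Section 1.2 expects that variability could change, partly through reduced carotid body activity. Section 2.10 correlates the changes in BP, RVV and EVV with the change in RCBA, and says this "will be performed as percentage of change".

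**The concern.** There are two problems with one primary outcome.

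**Definition.** An average of three tests, a lowest value and a reduction from baseline are not the same variable, and they do not all point the same way. More carotid body activity makes a reduction larger but an absolute nadir lower. An absolute nadir also follows resting ventilation itself. The text does not say whether the lowest value is the nadir within a test or the lowest of three tests, nor whether a reduction is in L/min or per cent. If this is settled after the data are seen, a primary outcome has been chosen by its result.

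**Variability.** The minimum of several short averages lies below a long average by chance, and further below when breathing is more variable. The trial expects variability may change under meditation and then correlates that change with the change in RCBA. Part of any such correlation would come from how the index is built.

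**Working it through.** The plan gives no figure to reproduce, and no coefficient of variation (CV), mean ventilation or response size usable here. Those are assumptions below.

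**1. The readings side by side.** Suppose ventilation is 10 L/min at week 0 and 9 L/min at week 8, and hyperoxia lowers it by 2 L/min each time. The absolute nadir goes from 10 − 2 = 8 to 9 − 2 = 7 L/min, which looks like more activity. The reduction is 2 L/min both times, which is no change. The rule for combining tests matters too. In a breath-level simulation with no response (10 L/min, 15 breaths/min, breath-level CV 20%, lag-1 autocorrelation 0.3), the reduction is 1.75 L/min averaged over three tests and 2.76 as the largest of three. The nadir is 8.25 averaged and 7.41 as the lowest of three.

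**2. Bias with no response.** Assume 10 L/min, six independent 10-second averages per minute, and a CV of these averages of 5%, 10% or 15% (SD 0.5, 1.0 or 1.5 L/min). The expected minimum of six standard normal values is −1.27. The expected index is therefore 1.27 × SD:

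- CV 5%: 0.63 L/min
- CV 10%: 1.27 L/min
- CV 15%: 1.90 L/min

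Averaging three tests reduces noise but leaves this expectation unchanged. A 20% fall in variability from CV 10% moves the index by 0.2 × 1.27 = 0.25 L/min. A 60-second mean minus a 60-second mean has expectation 0 at every CV.

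The pattern does not depend on independent windows. In the breath-level model, at breath-level CV 10% (a different scale from the CV above), the null index is 0.76, 0.87 and 0.94 L/min at autocorrelation 0, 0.3 and 0.6. A rolling 10-second window gives more (1.04 at 0.3).

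**3. Bias with a real response.** Assume a transient dip with relative depth 0, 0.5, 1, 1, 0.6 and 0.3 over the six windows, and a true peak of 2 L/min. Simulated, averaged over three tests:

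| CV of 10-s averages | 60-s mean minus 10-s nadir | 60-s mean minus 60-s mean |
|---|---|---|
| 5% | 2.30 | 1.13 |
| 8% | 2.55 | 1.13 |
| 10% | 2.74 | 1.13 |
| 15% | 3.28 | 1.13 |

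At CV 10% the bias is 2.74 − 2 = 0.74 L/min. A 20% fall in variability (10% to 8%) moves the index by 2.74 − 2.55 = 0.19 L/min, about 7% of it. With a 3 L/min peak the bias is about 0.65 and the shift about 0.16. The mean contrast does not move with CV. Its value is 2 × (0 + 0.5 + 1 + 1 + 0.6 + 0.3)/6 = 1.13.

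**4. Built-in correlation.** Hold the response constant, draw each visit's CV from 10% ± 2 percentage points, and estimate variability from the 30 ten-second averages in a five-minute recording. The change in the nadir index then correlates with the change in estimated variability at 0.41 with no response and 0.32 with the 2 L/min dip. With the mean contrast the correlation is about 0 in both cases.

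**The case against.** **A coherent reading exists.** A baseline is defined, a nadir is taken in each test, three tests are averaged, and the result is read as a reduction. On this reading the lowest value simply restates the nadir. It is the most natural reading, and a fuller protocol may state it. But the article never does, and its adjacent sentences conflict on a primary outcome. A one-sentence clarification would settle this part; it would leave the variability bias in place.

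**The no-response figures are near the upper end.** The trial presumes tonic carotid body hyperactivity, and with a real dip fewer windows compete for the minimum. That stands: the bias falls from about 1.3 to about 0.7 L/min. If the true response also varies between visits (SD 0.5 to 1.0 L/min), the correlation falls to about 0.18 to 0.27 for a 2 L/min dip.

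**Randomisation protects the comparison in part.** A bias common to both arms cancels. This stands, so the arm comparison suffers only if variability changes differently between arms. That is the change the secondary outcomes look for. The plan fixes no direction, so the bias could hide an effect as well as create one.

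**Two stronger readings are not supported.** A reader might infer that the plan would declare mediation from an artefact. Section 2.10 plans Pearson correlations to explore changes and no mediation model, and section 1.2 calls the study exploratory. A reader might also infer that percentage change fails because the index can approach zero. The nadir index has a positive floor even with no response, so that argument is weak for it.

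**Conclusion.** The concern holds in two parts. The definition of RCBA in section 2.5.9 is inconsistent as printed. The contrast of a 60-second mean with a 10-second nadir is biased upward by an amount that grows with breathing variability. The existence and direction of the bias follow from the method. Its size rests on the assumed 10 L/min, the CV, the independence of windows and the shape and depth of the dip. The correlation also assumes that variability is measured as the SD of 10-second averages rather than by the planned Poincaré indices.

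This does not show that RCBA will be biased between arms, nor that an observed effect would be false. It shows that an RCBA difference, and above all an RCBA–RVV correlation, could not be attributed to the carotid body without a further check. Severity: should be fixed.

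**What to change.** 1. Define RCBA once: the pre-test 60-second mean ventilation minus the 10-second nadir during hyperoxia, in L/min, computed per test and averaged over the three tests. State whether the 10-second windows are fixed or rolling. Delete or reword the sentence on the lowest value.
2. Pre-specify an equal-window contrast (60-second normoxic mean minus 60-second hyperoxic mean, averaged over the three tests) as a sensitivity analysis for the arm comparison.
3. Use the equal-window contrast for the association of RCBA with RVV and EVV, in absolute changes, with arm and baseline in the model. Percentage change would not suit this contrast, because its expectation is zero when there is no response.

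The cost is wording and a few lines of code on signals already recorded. The drawback is that the mean contrast dilutes a transient dip (1.13 against a true peak of 2 L/min above), so both versions should be reported.

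Subtracting the same nadir statistic from a normoxic minute may be shown as a further sensitivity analysis but should not replace the index. It over-corrects when a response exists: at a 2 L/min dip the corrected value falls from 1.67 to 1.38 L/min as CV rises from 5% to 15%.
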